##### Sample/material

The material included in the systematic review will result from the literature search. Observations of children’s free play and development and testing of initial instrument ideas was based on small convenience samples of children. For evaluation of measurement properties of the laboratory assessment instrument and the staff-report instrument, we included 139 children aged 4–5 years in measurements on two occasions separated by 1–2 months and the kindergarten staff who work with them completed the questionnaires on these two occasions.

##### Analysis plan

For the systematic review, the studies identified will be screened and selected in line with the inclusion and exclusion criteria by two independent authors. Initially a title search will be undertaken, followed by abstract screening and full text screening. A valid reason will be given for excluded studies. The method of analysis will be a narrative review to capture the relevant information regarding validity and/or reliability of existing instruments. For River Challenge, we will determine test–retest, inter- and intratester reliability, as well as structural validity. Analyses of reliability will be performed in SPSS. Test–retest reliability will be assessed over 1–2 months using Bland–Altman plots showing potential learning effects (bias) and random variation (95% Limits of Agreement) [189] and ICCs derived from a two-way mixed model using a consistency definition [187, 190]. Inter- and intra-tester reliability will be based on video-scoring of 20 children, representative of the larger sample with respect to age, sex and performance. Assessors will rate the same videos on two occasions, from which within-subjects or between-subjects ICCs will be derived from two-way mixed models using a consistency definition (excluding variation for assessors and time, respectively) [187, 190]. Structural validity will be determined using Confirmatory Factor Analysis (CFA) [191] in Mplus. Using CFA, we will compare the data to the hypothesized measurement model and evaluate model fit using suggested model fit indices [192]. If the model fit is not acceptable, modification indices with theoretical justifications will be used to adjust the model. If the model is still not acceptable, Explorative Factor Analysis (EFA) will be used to explore alternative models. We will test for invariance across sex in the accepted model [191].

For the Children’s Involvement and Well-being in Movement, Play and Exploration Questionnaire, we will determine internal consistency, intra-tester reliability and structural validity. Internal consistency will be determined using McDonald’s Omega [193] on the separate constructs after validating the structure of the instrument. Intra-tester reliability will be determined using ICCs derived from a one-way mixed model using an absolute agreement definition [187, 190], based on scores on two occasions from the staff member who knows the children in a given department best. Given the design, it is not possible to separate measurement errors over time for children’s behaviours (test–retest reliability) and staff’s judgements (intra-tester reliability). Yet, given that there is no intervention in between of the two measurement timepoints, we regard significant changes in children’s behaviours over this short period less likely. Inter-tester reliability will not be assessed, as there are few staff members who know the children well enough to do this assessment. Structural validity will be determined using CFA as detailed above.

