##### Movement competence and creativity

Movement competence and creativity will be measured using the “River Challenge”, which is being developed for this project. A brief description of its rationale, development and evaluation is provided in Sect. "Analysis plan".

In the River Challenge, children will be invited to take part in three challenges. The first challenge (“Crossing the river”) is based on locomotor and balance skills and the second challenge (“Rescuing the elephants”) on object control skills. In addition, each challenge will capture children’s creativity in and through movements, with a final challenge (“Creating an animal playground”) based on free play to capture creative thinking. The focus of the instruments is on adaptation of these skills to successfully achieve the challenges, rather than measurement of specific skills. Each challenge is presented as a story based on rescuing a variety of animals. This idea is based on Conceptual Playworlds [99], which is a method encouraging children to interact with stories that are personally meaningful to them, rather than responding to adults’ direct instructions. This method encourages adaptability and creativity as there are no specific methods/skills required to be used.

The challenges will be set up within the children’s daily kindergarten setting. The maximum space required will be 2 × 3 m to make it feasible for field testing. The children will be tested one-by-one to capture their own personal skilfulness, adaptability and creativity, rather than being influenced to provide solutions by others. Thus, tests will be conducted in a separate room or space. Tasks will be completed in a standardised order, using approximately 20 min per child. The test teams will consist of one instructor who tells the story, while a separate assessor observes and scores the child’s performance. Both challenges have eight levels (i.e., items), which will be scored based on successful or unsuccessful achievement. There will be no specific method/skills required to achieve each challenge, however detailed and standardized descriptions of what is ‘successful’ and ‘unsuccessful’ will be a fundamental aspect of the scorers' training. Scores are summed for each item and challenge.

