###### Main and secondary outcomes

Given that the broad MoveEarly intervention is targeted at promoting whole-child development, designating one primary outcome a priori is challenging. As a single test is not capable of capturing multiple aspects of a child’s development, we will determine effects across multiple relevant outcomes. Whilst regarding children’s movement competence and creativity as priority outcomes, we are cautious about defining the River Challenge as the main outcome given its unknown measurement properties and lack of data to allow a sample size calculation. If the River Challenge demonstrates acceptable measurement properties, we will designate movement competence and creativity as the main outcomes, and other aspects of children's development as secondary outcomes.

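### The planned inter-tester ICC for the River Challenge cannot register systematic leniency differences between assessors, and no other check for them is stated

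*Protocol article*

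**What the plan says.** The analysis plan under the development of measures (protocol article) sets the reliability work for the River Challenge. "Inter- and intra-tester reliability will be based on video-scoring of 20 children", with assessors rating the same videos twice. The ICCs come from "two-way mixed models using a consistency definition (excluding variation for assessors and time, respectively"). The number of assessors is not given.

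For test-retest reliability the same paragraph adds "Bland–Altman plots showing potential learning effects (bias) and random variation". It states no corresponding bias check for inter-tester scoring.

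Three other places bear on how the result is used:

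- Movement competence and creativity: the child is tested by a team in which "a separate assessor observes and scores" the performance. Item scores are summed.
- Primary aim, under the analysis plan of the outcome evaluation: the mixed models account for participant and kindergarten, and the primary analysis adjusts for the baseline level of the outcome only. No assessor term is stated.
- Main and secondary outcomes: "If the River Challenge demonstrates acceptable measurement properties, we will designate movement competence and creativity as the main outcomes". No numerical threshold is attached.

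**The concern.** A reliability coefficient should reflect the way the score is used. Here the trial uses the raw sum from whichever assessor tested the child. If one assessor credits success or originality more readily than another, that difference is part of the child's score and nothing stated in the analysis removes it. The question is therefore whether assessors give interchangeable scores.

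A two-way consistency ICC answers a different question: whether assessors rank and space the children alike once each assessor's own mean has been taken out. It can be high when the assessors' levels differ a good deal. Because the result contributes to the choice of main outcomes, a coefficient that cannot see this kind of error gives an incomplete basis for that choice.

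**Working it through.** The documents state no inter-tester ICC, assessor variance or acceptance threshold, so there is no figure of the plan's own to reproduce. The check compares the two definitions, using assumed values that are marked as such.

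**Definitions** (single rating; C = child variance, E = residual variance, A = assessor variance):

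- Consistency: C / (C + E)
- Absolute agreement: C / (C + E + A)

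A is absent from the first formula, which is the whole point.

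**Illustration 1: variance components.** Assume C = 1 and E = 0.25.

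- Consistency: 1 / 1.25 = 0.80 for any A
- Agreement, A = 0.10: 1 / 1.35 = 0.74
- Agreement, A = 0.25: 1 / 1.50 = 0.67
- Agreement, A = 0.50: 1 / 1.75 = 0.57

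**What these variances mean as offsets.** With two assessors who differ by a constant d, in units of the within-assessor score SD, agreement = consistency / (1 + d²/2). Matching the two forms gives d = √(2A / 1.25). The three assumed variances correspond to offsets of √0.16 = 0.40, √0.40 = 0.63 and √0.80 = 0.89 SD.

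**Illustration 2: what 20 videos would show.** Simulation of 10,000 data sets with 20 children, two assessors (assumed), true consistency ICC 0.85 (assumed) and an illustrative cut-off of 0.75 (assumed; the plan has none):

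| Offset (SD) | Mean consistency ICC | Mean agreement ICC | Consistency ≥ 0.75 | Agreement ≥ 0.75 |
|---|---|---|---|---|
| 0 | 0.84 | 0.84 | 88% | 88% |
| 0.25 | 0.84 | 0.81 | 89% | 81% |
| 0.5 | 0.84 | 0.74 | 89% | 51% |
| 0.75 | 0.84 | 0.65 | 89% | 15% |
| 1.0 | 0.84 | 0.55 | 88% | 1% |

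The consistency column does not move, so even a one-SD difference in leniency would not show in the planned statistic.

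**The bracketed clause.** It is unclear what its closing word pairs. Read against the order of inter- and intra-tester earlier in the paragraph, assessor variation is excluded from the inter-tester ICC. Read against the order of within- and between-subjects in the same sentence, time may be what is excluded from the inter-tester ICC. On either reading, a consistency ICC computed across assessors drops their mean differences. If the intention was to keep assessor variation in the error, the consistency definition contradicts it.

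**The case against.** The strongest reply is that assessor offsets may be small. Movement items are scored as success or failure against standardised descriptions, and scorer training is built around them. The section on data management and quality control also promises thorough training and says that inter-tester reliability will be assessed for observational measures. This lowers the likely size of the problem, especially for movement competence. It does not remove it: that section names no statistic, training limits offsets without measuring them, and fluency and originality scoring for creativity leaves more to judgement.

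Four stronger readings are tempting, and the documents do not support them.

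- *The test will be wrongly made the main outcome.* Test-retest reliability, intra-tester reliability and structural validity are evaluated too, and the condition "If the River Challenge demonstrates acceptable measurement properties" has no threshold. The inter-tester ICC is one input.
- *Assessor error raises the kindergarten-level ICC and lowers power.* That needs assessors to be aligned with kindergartens. Their number and allocation are not stated. If they rotate, leniency is mostly noise between children.
- *The two new instruments are held to different standards*, since the staff questionnaire is assessed "using an absolute agreement definition". That is a one-way, intra-tester design with raters who differ between departments. It is no benchmark for assessors who all rate the same videos.
- *Test-retest reliability needs absolute agreement as well.* The Bland-Altman analysis already planned there shows systematic shift.

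It is also fair to say that this is an instrument-validation analysis whose details are deferred to a separate paper. But the article does fix the ICC definition, and the result feeds a decision about this trial.

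**Conclusion.** The point holds in a limited form. The planned inter-tester coefficient cannot detect systematic differences between assessors, no other stated check does so for inter-tester scoring, and the trial's use of single-assessor raw sums makes such differences relevant. In the illustration a consistency ICC of 0.80 goes with an agreement ICC anywhere from 0.74 to 0.57. Those figures rest entirely on assumed variances; the larger ones imply offsets of 0.63 to 0.89 SD, which nothing in the documents shows to be likely. With no offset the two coefficients coincide. This is a cheap improvement to the evidence behind the choice of main outcomes. It does not show that the instrument is unreliable or that the trial's comparison is biased.

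**What to change.** For inter-tester reliability of the River Challenge, report a two-way, absolute-agreement, single-rater ICC with its 95% interval, together with the mean difference between assessors, for movement competence and for creativity. The consistency ICC can stay beside it. Name the absolute-agreement value and the mean difference as the inter-tester evidence used in the main-outcome decision. Reword the bracketed clause so that it is clear which source of variation is left out of which coefficient. The test-retest plan can stay as it is.

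The cost is small: the same video ratings are re-analysed and no new data are needed. The reported coefficient will generally be equal or lower. With few assessors, assessor variance is poorly estimated and the interval will be wide, so the value should be read with its interval and the mean difference, not as a single pass mark.

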### Process evaluation

Given that MoveEarly is framed within a “realist RCT” approach [73], a complex systems perspective will be used to explore the deeper (sociological) mechanisms by which the kindergartens interact with the intervention [68]. The initial program theory, described in Sect. " Intervention and theoretical framework", states that by enhancing staff competence and motivation to integrate the move-play-explore pedagogy into kindergarten’s daily operations, we expect to find positive effects on children’s health, development, well-being, and learning. This causal pathway, and how it varies according to individual and contextual factors, will be examined in the process evaluation, which seeks to provide a general overview as well as a deeper insight into how staff and children in the intervention kindergartens respond to the MoveEarly professional development and integrate the move-play-explore pedagogy into staffs’ and children’s daily practices. Thus, the process evaluation will explore what works for whom, under what circumstances, and why, within the MoveEarly intervention. As suggested by McGill et al. [194], we will use a 2-phase framework for the process evaluation that seek to assess change over time from a complex systems perspective. The first phase will involve producing a description of the system and identifying hypotheses about how the system change in response to the MoveEarly intervention. The second phase will involve adapting the planned evaluation approach in accordance with the pathways of the emergent findings.

#### Samples and methods

The process evaluation will draw on multiple methods to triangulate data and user perspectives [78] and includes four samples. The first sample includes all kindergartens participating in the study (i.e., both intervention and control), the second sample includes all intervention kindergartens, the third sample includes selected kindergartens invited to take part in a multi-site case study (i.e., both intervention and control), and the fourth sample includes only the intervention kindergartens taking part in the multi-site case study. While the research including all kindergartens will test between-group effects and describe implementation measures in the MoveEarly intervention, the multi-site case study will use an ethnographic approach to provide an in-depth understanding of how the intervention evolves and builds momentum in kindergartens [195]. An overview of the methods and timelines for the data collection in the process evaluation is provided in Fig. 5.

**Fig. 5 Fig5:**
[figure not shown]
The timeline of the data collection in the process evaluation

##### Sample 1: All kindergartens

Data collection in sample 1 includes a questionnaire about the kindergarten’s leadership and organization, a questionnaire about the kindergarten’s pedagogical practices and measurement of staff PA levels.

Kindergarten’s leadership and organization will be assessed by a questionnaire completed by directors at baseline and at 24-month follow-up. Focus areas are staff’s perceptions of the national policy, their local context and the kindergarten’s daily organization. The baseline questionnaire will be used to sample kindergartens to the multi-site case study.

Self-assessment of pedagogical practices will be performed by pedagogical leaders of each department using a brief custom-made questionnaire, guided by the pedagogical principles of the intervention (Sect. "Child level – A move-play-explore pedagogy") and a custom-made environment rating scale developed to assess pedagogical practices by researcher observation (Sect. "Sample 3: Multi-site case study"). The questionnaire has 25 items assessing the kindergarten’s indoor physical environment (items 1–6), the kindergarten’s outdoor physical environment (items 7–12) and the kindergarten’s pedagogy (items 13–25) and will be completed at baseline, 12- and 24-month follow-up.

Staff’s PA level will be assessed using accelerometry, performed simultaneously with the three child measurements at baseline, 7- and 18-month follow-up. We will use the same procedures as detailed for children, except using another criterion for non-wear time (≥ 60 min of zero counts) and using the commonly applied adult Troiano cut points to determine intensity-specific PA (SED < 100 cpm, LPA 100–2019 cpm, MPA 2020–5998 cpm, VPA ≥ 5999 cpm, and MVPA ≥ 2020 cpm) [196]. Data will primarily be analysed using short epochs (1 s) to allow for capturing short intermittent bursts of PA consistent with children’s activity patterns, but we will also use 60-s epochs for comparison with previous adults studies [197, 198].

##### Sample 2: Intervention kindergartens

Data collection in sample 2 includes written work by staff submitted as part of the professional development, registration of adherence to the professional development, multiple short implementation questionnaires and a project evaluation questionnaire. Contact points between researchers and kindergartens will be logged.

Several types of written work (project plans, reflection papers and project reports) will be collected from the kindergarten internal project group to assess the visibility and formalisation of the MoveEarly intervention in the intervention kindergartens. Project plans will include each kindergartens’ own aims for the development work, the planned approach to integrate the MoveEarly pedagogical principles into their daily practice (e.g., whether principles and/or activities will expand, extend and/or enhance children’s opportunities [84]) and a description of the organization of the process, including milestones, leadership and responsibilities. Reflection papers will include a discussion about children’s and staff’s experiences with the move-play-explore pedagogy in relation to the pedagogical principles based on plans, videos, pictures and/or observations. Project reports will include staff’s reflections regarding their experiences of successes and challenges during implementation of planned aims, pedagogical approaches and institutional organization, with the overarching aim of developing action points for improved future practices.

Adherence to the professional development will be registered throughout the intervention period. These data will include attendance to all physical and digital meetings and submitted written work. Additionally, researchers will score each kindergarten on a 5-point Likert scale in terms of the 1) director’s and project group’s leadership and 2) staff engagement. Primary focus areas will be level of concretization of tasks, plans and milestones in written work and meetings, and involvement of all staff members in implementing the intervention.

The kindergarten project group will complete multiple short questionnaires to rate their experience of collaboration with researchers, resources provided them, and implementation of the intervention in their kindergarten, at all physical seminars except for the kick-off. Questions will be tailored on each occasion according to formal and informal feedback from kindergartens during the project period.

At 24-month follow up, the kindergarten internal project group will be asked to complete an evaluation questionnaire. The following three domains will be examined: 1) Implementation, 2) mechanisms of impact and context and 3) sustainability of the new practice in the kindergartens’ daily operations [199]. Specifically, we will assess how staff experienced participation in the intervention, including their experience with the move-play-explore pedagogy, satisfaction with the professional development, digital resources, and collaboration with researchers, as well as barriers and facilitators of their kindergarten’s development work. The questionnaire will be informed by researchers’ experiences with running the professional development and preliminary findings from the process evaluation.

##### Sample 3: Multi-site case study

We will purposively sample 8 intervention kindergartens and 4 control kindergartens to participate in the multi-site case study. Kindergartens will be sampled for diversity in terms of the extent to which the kindergarten seems responsive to the intervention (assessed by baseline questionnaire and initial project description), urban and suburban locations, outside and inside facilities, and the kindergarten’s owner and profile. This approach allows a rich inquiry into intervention implementation in several different, naturalistic settings, and thus allow a more in-depth understanding of the phenomena than a single case can provide [200].

As the intervention relates both to the kindergarten staff and children, both groups will be included in the qualitative studies. In this way, we seek to better understand children’s whole bodily repertoires, and the conditions for them, when children move, play, or explore their environments. Considering children’s tendency in being enactive and easily engaging in activities, showing a genuine interest and enthusiasm (i.e., agency), we will study children’s behaviour as meaningful projects that extend out into the world and are deeply embedded with the environment. We will intertwine in our design both *child perspectives* and *children’s perspectives* as defined by Sommer, Pramling Samuelsson and Hundeide [201]. We understand *child perspectives* as “created by adults who are seeking, deliberately and as realistically as possible, to reconstruct children’s perspectives, for example through scientific concepts concerning children’s understanding of their world and their actions in it” [201] (p. 22). However, although “child perspectives attempt to get as close as possible to children’s experiential world they will always represent adults’ objectification of children” [201] (p. 22). The *children’s perspectives* on the contrary “refer to the perceptions of the non-adult subjects themselves” (p. 22), and capture children’s ‘here and now’ experiences, perceptions, and understandings of their physical and social environments.

A range of methods will be used to capture kindergarten practices, including staff, children’s and child perspectives:

 Staff observation of children

Observation is a significant part of kindergartens’ pedagogical practices [202–204] and may have a summative [204] or more dialogical [203] character in different ECE traditions. While the summative approach focuses children’s progress in development, the dialogical approach highlights a process of documentation that stimulates teachers' reflection over own practice [203] by trying to understand it from the perspective of the child/children [203, 205, 206]. The dialogical perspective rejects the accountability approach, while highlighting the importance of teachers’ subjectivity, reflection and meaning-making in attempting to widen and understanding children’s (re)actions and their own professional practice. The dialogical perspective is in line with the Nordic approach to ECE [202].

In Norway, the established methods for observation in ECE are a) continuous notes—*løpende protokoll*, b) story from practice—*praksisfortelling*, and c) participatory observation—*deltagende observasjon* [207]. What differs in these methods is the distinction between empirical notes and interpretation. While for *continuous notes* and *participatory observation* it is important to make notes as objectively as possible (and invite diverse interpretations in the next stage), *story from practice* allows for immediate subjective interpretations (e.g., while a teacher in continues notes would note a child is smiling, a story from practice would note a child being happy). In line with the technological development, the ECE sector has also made use of video-based observation, which allows for a more objective understanding of their own practices both from professional, ethical and child perspectives [208]. This approach turns out to be particularly beneficial in evaluation of complex interactions [209] and for self-evaluation [210] and self-reflection [211].

While we recommend video-observations, continuous notes or participatory observation, teachers will be allowed to choose among different observation methods to maximize chances of gathering observational data. Regardless the chosen observation method(s), teachers will be asked to:Choose 2 children with different needs; (*a*) a child who easily engages in activities and *b*) a child who often needs extra support to participate in activities.Conduct observations on the children’s experiences of the move-play-explore pedagogy 3 times a week over a period of 2 months towards the end of the first and second years of interventionShare their interpretations of the children’s experience during the interview following the guided tours.

 «Guided Tour»—video-based observation of situated practices

Guided tour is a participatory research technique developed for studying embodied and situated knowledge/experience [108, 109]. The participant(s) are positioned in the roles of experts who guide the researcher around a space that is familiar and professionally or personally meaningful for them. The researcher is positioned as a visitor totally dependent on the participant(s)’ knowledge to move around the visited space. Such positioning gives the researchers possibility to access deeply situated and embodied knowledge, mediated through the stories, actions and body language of the research participants. Video and audio recording of such visits allows to document the verbal and nonverbal storytelling on the “local ecologies” [110], revealing the way the participants interact and experience the space, and what meanings they attach to different areas.

In MoveEarly, the guided tours will be implemented to access the embodied, situated and practiced understandings of the project’s main concepts: *movement, play, and exploration*. In each kindergarten, 1–2 of the kindergarten staff together with minimum 3 children in 2 different departments will guide the researchers around and show, tell, and demonstrate how and where they move, play, and explore. Studying the verbal-nonverbal interactions among participants and the surroundings, will allow researchers to reflect on the embodied, situated, lived, and practiced understandings of the concepts move, play, and explore and thus support development of the pedagogical design. The guided tours will be informed by the guided tours performed in the conceptual groundwork for pedagogical design (4.1.1.2) and other parts of the process evaluation where change of the kindergartens’ conceptualisations of move-play-explore will be investigated. After the tour, focus groups with kindergarten staff will allow us to study staff’s reflection over the places/spaces, activities and understanding that appear and become visual/verbal during the guided tour.

 Children’s drawings

As the children are important actors in the kindergarten context, we need to develop ways of capturing their experiences. Being aware that the verbal code is only one, and often not the optimal, way for children to express their experiences and meanings, we will employ drawing as a method that allows another form of expression [212, 213]. Since drawing is one of the kindergartens’ daily activities, it will not take children away from their daily life in the kindergarten into, for example, an artificial interview setting. It will capture children’s experience of the kindergarten activities, through a salient, familiar activity. Once a week over two months in the end of the first and second intervention years, preschool children (i.e., last year of the kindergarten) will be asked to draw “the most joyful activity that they have participated in during this week”. The drawings will create a base of visual data documenting children’s perception of their best activities, including moments of move-play-explore as (hopefully) implemented in the daily kindergarten practice.

 Observation of the movement environment

We will use a custom-made observation instrument specifically capturing the move-play-explore pedagogy to quantitatively assess staff’s pedagogical practices. This instrument will be based on the pedagogical principles underpinning the child level intervention (Sect. " Child level – A move-play-explore pedagogy") and will focus on observable indicators, as information received from staff logs or interviews is difficult to obtain and may introduce errors. The instrument includes 8 items and assesses 2 dimensions of the environment: Physical enrichment (items 1–4) and Child-staff-interactions (items 5–8). Each item is scored from 1 to 7 based on multiple indicators, equivalent to the Movement Environment Rating Scale [214] and other similar environment rating scales. Observations will be performed by trained researchers for a full day (08:30–15:30) within each kindergarten department. More details about the instrument will be published in a separate paper.

